**Secondary outcomes (cognitive functioning): the tools and the evaluation procedures**
Trail Making Test [31]: it is a widely administered neuropsychological assessment tool designed to evaluate cognitive flexibility, visual attention, and processing speed. It consists of 2 parts: TMT-A, which requires participants to connect numbered circles sequentially, and TMT-B, which alternates between numbers and letters, assessing more complex executive functions such as task-switching and set-shifting. Reliability studies have reported Cronbach α values ranging from 0.70 to 0.89, depending on the sample characteristics and testing conditions. The questionnaires will be administered following this timeline: T0 (0 weeks), T1 (6 weeks), T2 (12 weeks from T1), T3 (24 weeks from T1), T4 (36 weeks from T1), and T5 (48 weeks from T1).Digit Span [32]: it is a neuropsychological test used to evaluate working memory, attention, and immediate verbal memory. It consists of 2 components: Digit Span Forward, which evaluates simple attention and memory span by requiring participants to repeat a sequence of numbers in the same order, and Digit Span Backward, which assesses working memory and cognitive flexibility by requiring participants to repeat the sequence in reverse order. Reliability studies have reported Cronbach α values ranging from 0.70 to 0.90, indicating good internal consistency across different populations and testing contexts. The test will be administered following this timeline: T0 (0 weeks), T1 (6 weeks), T2 (12 weeks from T1), T3 (24 weeks from T1), T4 (36 weeks from T1), and T5 (48 weeks from T1).Stroop Test [33]: it is a widely used neuropsychological test that measures cognitive control, selective attention, and processing speed. It evaluates the ability to inhibit automatic responses and resolve cognitive interference by requiring participants to identify the ink color of a word that may denote a different color name (eg, the word “red” printed in blue ink). The test typically includes 3 conditions: “reading colour names,” “naming coloured blocks,” and “naming the ink colour of incongruent colour-word pairs.” The Stroop effect, reflected in the increased time or errors during the incongruent condition, provides insights into executive functioning and attentional control. Cronbach α values reported in reliability studies range from 0.72 to 0.91, depending on the version of the test and the characteristics of the population studied. The test will be administered following this timeline: T0 (0 weeks), T1 (6 weeks), T2 (12 weeks from T1), T3 (24 weeks from T1), T4 (36 weeks from T1), and T5 (48 weeks from T1).Rey Figure Test [34]: it is a neuropsychological assessment that measures praxis abilities, visuospatial abilities, working memory, long-term memory, and executive functions. The test involves having a person first copy a complex drawing and then reproduce it from memory after a delay. Studies have reported varying Cronbach α values, but they generally indicate adequate internal consistency for the Rey Figure Test scoring methods. The test will be administered following this timeline: T0 (0 weeks), T1 (6 weeks), T2 (12 weeks from T1), T3 (24 weeks from T1), T4 (36 weeks from T1), and T5 (48 weeks from T1).Frontal Assessment Battery (FAB) [35]: it is a brief neuropsychological assessment instrument designed to evaluate executive functions and cognitive processes associated with frontal lobe activity. It consists of 6 subtests assessing different aspects of executive function: conceptualization, mental flexibility, motor programming, sensitivity to interference, inhibitory control, and environmental autonomy. Studies have reported Cronbach α values ranging from 0.78 to 0.90, indicating good internal consistency across various populations. The test will be administered following this timeline: T0 (0 weeks), T1 (6 weeks), T2 (12 weeks from T1), T3 (24 weeks from T1), T4 (36 weeks from T1), and T5 (48 weeks from T1).Matrix Test [36]: it is a cognitive assessment tool designed to evaluate nonverbal reasoning, abstract thinking, and problem-solving abilities. It typically involves identifying patterns or completing sequences in visual matrices. The reliability of the Matrix Test, as indicated by Cronbach α, generally ranges from 0.80 to 0.90, reflecting good to excellent internal consistency. The test will be administered following this timeline: T0 (0 weeks), T1 (6 weeks), T2 (12 weeks from T1), T3 (24 weeks from T1), T4 (36 weeks from T1), and T5 (48 weeks from T1).Rey Word Test [37]: it is a neuropsychological measure designed to assess verbal memory performance and identify potential malingering through tasks involving the recall and recognition of word lists. The Cronbach α falls within a range of 0.70 to 0.85, depending on the specific population and administration conditions, indicating acceptable to good internal consistency. The test will be administered following this timeline: T0 (0 weeks), T1 (6 weeks), T2 (12 weeks from T1), T3 (24 weeks from T1), T4 (36 weeks from T1), and T5 (48 weeks from T1).Addenbrooke’s Cognitive Examination-Revised (ACE-R) [29]: it is a brief tool used for the assessment of 5 key cognitive domains: attention and orientation, memory, verbal fluency, language, and visuospatial abilities. The test has a maximum score of 100, with a recommended range of 66.93-84.93 for the detection of mild cognitive impairment. Notably, ACE-R incorporates the Mini-Mental State Examination (MMSE) as part of its structure. The test will be administered following this timeline: T0 (0 weeks), T1 (6 weeks), T2 (12 weeks from T1), T3 (24 weeks from T1), T4 (36 weeks from T1), and T5 (48 weeks from T1).
**Tertiary outcomes (psychosocial and physical functioning): the tools and evaluation procedures**
Short Form Health Survey-12 item (SF-12) [38,39]: it assesses the following dimensions of well-being and quality of life: vitality, physical functioning, bodily pain, general health perception, mental, physical, and emotional health, work functioning, and social role. The total score ranges from 12 to 47, with higher scores indicating better quality of life. The test will be administered following this timeline: T0 (0 weeks), T1 (6 weeks), T2 (12 weeks from T1), T3 (24 weeks from T1), T4 (36 weeks from T1), and T5 (48 weeks from T1).Patient Health Questionnaire-9 (PHQ-9) [40]: it assesses the presence and severity of 9 depressive symptoms experienced over the past 2 weeks, including depressed mood, anhedonia, sleep and appetite disturbances, low energy, difficulty concentrating, psychomotor disturbances, loss of self-esteem, and suicidal ideation. The total score ranges from 0 to 27, with higher scores indicating greater severity of depressive symptoms. The test will be administered following this timeline: T0 (0 weeks), T1 (6 weeks), T2 (12 weeks from T1), T3 (24 weeks from T1), T4 (36 weeks from T1), and T5 (48 weeks from T1).Generalized Anxiety Disorder-7 item (GAD-7) [41]: it assesses the presence and severity of 7 anxiety symptoms experienced over the previous 2 weeks, including nervousness, inability to stop worrying, excessive worry, restlessness, difficulty relaxing, irritability, and fear that something awful might happen. Scores range from 0 to 21, with higher values reflecting more severe anxiety symptoms. The test will be administered following this timeline: T0 (0 weeks), T1 (6 weeks), T2 (12 weeks from T1), T3 (24 weeks from T1), T4 (36 weeks from T1), and T5 (48 weeks from T1).Brief Social Rhythms Scale (BSRS) [42]: it assesses the (ir)regularity of rhythms over the past week using 10 items. It evaluates sleep (wake-up and bedtime), eating habits (across different meals), and social interactions (eg, work and/or leisure activities). Scores range from 10 to 60, with higher scores indicating poorer rhythm regularity. The test will be administered following this timeline: T0 (0 weeks), T1 (6 weeks), T2 (12 weeks from T1), T3 (24 weeks from T1), T4 (36 weeks from T1), and T5 (48 weeks from T1).Physical Body Experiences Questionnaire Simplified for Active Aging (PBE-QAG) [43]: it assesses body awareness over the past month, focusing on 4 dimensions using 12 items: relationship with one’s own body, body acceptance, awareness of physical abilities, and awareness of physical limitations. Scores range from 12 to 60, with higher scores indicating lower overall body awareness. The test will be administered following this timeline: T0 (0 weeks), T1 (6 weeks), T2 (12 weeks from T1), T3 (24 weeks from T1), T4 (36 weeks from T1), and T5 (48 weeks from T1).International Physical Activity Questionnaire (IPAQ) [44]: it assesses the type and amount of physical activity performed over the past 7 days, including both work-related and leisure activities, using 9 items. The total score is based on the conventional unit of measure “MET,” where higher MET corresponds to higher levels of physical activity. The test will be administered following this timeline: T0 (0 weeks), T1 (6 weeks), T2 (12 weeks from T1), T3 (24 weeks from T1), T4 (36 weeks from T1), and T5 (48 weeks from T1).Sway area in the presence and absence of visual input [45]: it assesses the quantitative balance maintenance abilities under static conditions. The evaluation will be conducted under 2 conditions: eyes open and eyes closed. Participants will be asked to step onto the platform barefoot and remain as still as possible for 30 seconds. The test will be repeated 3 times for each condition. This assessment will be administered according to the following timeline: T0 (baseline, 0 weeks) and T1 (6 weeks).Gait speed analysis (GA) [46]: it assesses the analysis of gait, using a miniaturized wearable inertial sensor. The sensor is positioned on the lumbar region of the trunk at the level of vertebrae L5-S1. The participant is asked to walk at a comfortable, self-selected speed along a straight, unobstructed path of at least 2 m. This assessment will be administered according to the following timeline: T0 (baseline, 0 weeks) and T1 (6 weeks).Timed-Up-and-Go (TUG) [47]: it assesses the functional mobility in older adults. The test involves standing up from a chair, walking for 3 m, turning around an obstacle, returning to the starting point, performing a 180° turn, and sitting back down. The participants will perform an instrumented version of the TUG using a wearable inertial sensor placed on the lower back at the level of vertebra L2. This assessment will be administered according to the following timeline: T0 (baseline, 0 weeks) and T1 (6 weeks).

### Data Management and Security

The main goal of the data management process is to guarantee the timely delivery of high-quality data in order to meet the requirements of appropriate statistical analysis. It includes all phases of data management, such as data collection, processing, and application. Clinical data will be compiled into a structured longitudinal database to ensure consistency and facilitate research activities. Each participant will be assigned a unique identification number at the start of the study. The study will be conducted following the Declaration of Helsinki [48] and the requirements of all applicable local and international standards, according to data protection laws.

### Adverse Event Reporting

Each adverse event will be documented with detailed information, including the type of event, onset and resolution dates, severity, expectedness, outcome, and its potential relationship to the study.

### Data Analysis, Statistical Power, and Sample Size

The statistical analysis will use SPSS software (version 21; IBM Corp). Descriptive statistics will be calculated for all variables, with nominal variables reported as frequencies and percentages (n; %) and continuous variables as means and SDs (mean, SD).

Given the feasibility-oriented nature of this trial, all analyses of secondary and tertiary outcomes are exploratory and are not intended to provide definitive evidence of effectiveness. The inclusion of multiple cognitive, psychosocial, and physical outcomes is justified by the need to obtain preliminary effect size estimates and variability parameters that will guide the selection and prioritization of outcomes in a future fully powered RCT. Therefore, the analyses of secondary and tertiary outcomes will be interpreted as hypothesis-generating. No formal power calculations for effectiveness end points have been performed, as the current sample size is intended to assess procedural feasibility and parameter estimation rather than hypothesis testing.

To assess baseline homogeneity between the control group and the intervention group, chi-square tests will be used for nominal variables and 1-way ANOVA for continuous variables. Expected differences related to “group,” “time,” and the “group × time” interaction for all dependent variables will be analyzed using a series of multivariate ANOVA. Specifically, repeated-measures ANOVA and multivariate ANOVA will be applied to continuous variables, while the De Castellan test will be used for nominal variables. Bonferroni correction will be applied where appropriate. The assumption of normality for dependent variables will be examined in relation to sphericity, with the Mauchly test used to assess the equality of variances across related group combinations. Cases with missing data will be treated as incomplete and excluded from the analyses. Secondary analyses may be conducted on specific subgroups (eg, by age) and on selected outcomes (eg, individual items from the administered questionnaires).

Regarding statistical power, it is important to note that no previous RCTs have examined the effects of an immersive VR intervention using virtual sailing scenarios in this population. For this reason, this study is designed as a feasibility and exploratory trial. Although this, the planned sample size is consistent with previous feasibility studies using VR-based paradigms, which have typically enrolled small to moderate cohorts [18,46-48]. On this basis, a total sample of 40 participants (20 per arm) was considered appropriate to assess procedural feasibility, obtain reliable estimates of variability, and capture preliminary effect size signals to inform the design for a fully powered RCT.

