## Results

This project was initially funded in 2022 for a planned duration of 2 years. A 12-month extension was requested and subsequently granted due to delays in the recruitment and implementation phases. Particularly, recruitment was slowed by post–COVID-19 challenges: given the advanced age and MCI of the target population, regular access to the participating health care facilities and engagement in the study were not always feasible. Furthermore, the intervention was originally designed to be delivered through a sailing navigation simulator based on semi-immersive VR technology, which required a dedicated physical environment. Persistent logistical barriers in securing a suitable setting led the research team to develop and adopt a more advanced immersive VR device, which preserved the original study objectives but required additional time before submission and approval by the Ethics Committee.

Recruitment activities began in May 2024 and are planned to be completed by November 2025. As of manuscript submission, 153 participants were recruited and screened regarding inclusion and exclusion criteria. Among them, 39 participants have been enrolled. Preliminary pre-post analyses are scheduled for January 2026; follow-up analyses will be completed by January 2027.

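### The secondary and tertiary outcomes are meant for estimation, but the plan fixes group, time and group × time tests without baseline adjustment, plus significance tests of baseline balance

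*Protocol article*

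**What the plan says.** All of the analysis text is in the protocol article, Data Analysis, Statistical Power, and Sample Size.

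- **Purpose.** The many secondary and tertiary outcomes are "justified by the need to obtain preliminary effect size estimates and variability parameters that will guide the selection and prioritization of outcomes" for a later trial. The sample size is "intended to assess procedural feasibility and parameter estimation rather than hypothesis testing".
- **Method.** For the group, time and group × time effects, the "interaction for all dependent variables will be analyzed using a series of multivariate ANOVA"; more specifically, "repeated-measures ANOVA and multivariate ANOVA will be applied to continuous variables". No baseline covariate, between-arm contrast, reference visit or confidence interval is named. Means and SDs are planned for continuous variables.
- **Baseline.** "To assess baseline homogeneity between the control group and the intervention group, chi-square tests will be used for nominal variables and 1-way ANOVA for continuous" ones.

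Three facts from other sections matter. Randomization and Allocation Concealment places randomisation after the baseline assessment. Textbox 1 has every secondary and tertiary outcome measured at T0, most at all six visits, but sway area, gait and Timed-Up-and-Go only at T0 and T1. Results states: "Preliminary pre-post analyses are scheduled for January 2026".

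**The concern.** The stated aim is to estimate, but the methods named are tests. A later trial needs, for each candidate outcome, a signed between-arm difference at a known visit and its uncertainty.

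The article does not say outright that T0 is a level of the time factor. It is the natural reading: time is a tested factor, all these outcomes are measured at T0, the first analysis is pre-post, and no covariate is named. On that reading:

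- With T0 and T1, group × time compares change scores and gives up precision that T0 adjustment would recover.
- With all six visits, group × time is an omnibus test of whether the arms' profiles differ anywhere. It does not say by how much, in which direction or when.
- The group main effect averages in a visit at which no treatment effect can exist.
- The time main effect contains practice on repeated tests and, for ACE-R (both entry screen and outcome), regression to the mean. It is not evidence of benefit.

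The baseline tests are a separate matter. With concealed randomisation, any T0 difference is chance by construction. A test of it gives no useful information and does not correct the comparison.

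**Working it through.** The article gives no power calculation or effect size for these outcomes, so there is no figure to reproduce.

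**Inputs from the article:** n = 20 per arm, 1:1; visits T0 to T5; T0 before randomisation.

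**Assumptions not in the article:** T0–T1 correlation r = 0.5, 0.7 or 0.8; outcome SD 1 at each visit; two-sided 5% level; all 40 participants analysed. For six visits: equal correlations between visits and a constant effect d from T1 onward.

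**1. Two visits: group × time is the change-score test.** On one simulated data set of 40, the interaction F and the squared t on change scores were both 3.344.

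- Variance of the change-score difference: (2/n) × 2(1 − r).
- Variance of the T0-adjusted difference (ANCOVA): (2/n)(1 − r²), times 1 + 1/(2n − 4) = 1 + 1/36 = 1.028 for estimating the slope.
- Large-sample ratio: (1 − r²) / [2(1 − r)] = (1 + r)/2. The small-sample ratio is 1.028 times this.

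| r | (1 + r)/2 | with 1.028 | SE, change | SE, adjusted |
|---|---|---|---|---|
| 0.5 | 0.75 | 0.77 | 0.316 | 0.278 |
| 0.7 | 0.85 | 0.87 | 0.245 | 0.229 |
| 0.8 | 0.90 | 0.93 | 0.200 | 0.192 |

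The 95% half-widths use t = 2.024 (38 df) for change and 2.026 (37 df) for adjusted. They are 0.64 v 0.56 SD, 0.50 v 0.46 SD and 0.40 v 0.39 SD. As an equivalent sample size, 20/0.77, 20/0.87 and 20/0.93 give about 26, 23 and 22 per arm.

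Power at d = 0.5, group × time v adjusted: 34% v 42%, 51% v 57% and 68% v 72%.

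**2. Six visits: the interaction is an omnibus test.** Two arms by six visits give (2 − 1)(6 − 1) = 5 df. At d = 0.5 and r = 0.7 its power is 48% (univariate) or 43% (multivariate). A T0-adjusted contrast on the mean of T1 to T5 has 83%. That contrast is favoured by the assumed constant effect, so this is an illustration, not a general ratio.

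**3. Group main effect with T0 included.** The true difference at T0 is 0.

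- Two visits: (0 + d)/2 = d/2. A T1 effect of 0.5 SD appears as 0.25 SD, with about 13% power at r = 0.7.
- Six visits: (0 + 5d)/6 = 5d/6. The same effect appears as 0.42 SD.

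**4. Baseline tests.** For k independent tests at 5%, the chance of at least one significant result is 1 − 0.95^k: 54% for k = 15 and 64% for k = 20. The count and the independence are assumptions; the article does not list the variables tested.

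**The case against.** The strongest defence is that this is a feasibility trial, its secondary and tertiary analyses are declared exploratory, and a condensed article may leave contrasts and intervals to an analysis plan that is not shown. Much of this stands, and it rules out several stronger readings.

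- **A reader might infer that the baseline data are discarded or the comparison is biased.** Neither follows. Group × time uses T0 and, with two visits, corresponds to a signed, unbiased difference in change. Practice and regression to the mean are expected equally in both arms, so they do not bias it.
- **A reader might infer that the trial fails its main purpose.** Feasibility is the primary outcome. Effect estimation is the stated reason only for the secondary and tertiary outcomes.
- **A reader might infer that the group or time main effect will be reported as the treatment effect.** The article lists them as terms and does not say so; the dilution matters only if they are read that way.
- **A reader might infer that one multivariate model of all cognitive tests at all visits is planned, too large for 40 people.** The text speaks of a series of analyses and does not state a joint model.
- **A reader might infer that no estimates at all will be available.** Means and SDs, if given by arm and visit, would allow crude differences, though not the adjusted difference or its interval.

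The six-visit criticism also does not apply to the January 2026 pre-post analysis, nor to sway area, gait or Timed-Up-and-Go.

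The deferral argument does not dispose of the point. The article does not leave the method open: it names a less precise model and names baseline significance tests.

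**Conclusion.** The point holds as a mismatch between a stated aim of estimation and a stated set of unadjusted tests. It does not show that the trial is invalid.

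The size is modest and depends on correlations the article does not give. For the T0–T1 comparison, T0 adjustment cuts the variance by about 23%, 13% and 7% at r = 0.5, 0.7 and 0.8, and it helps less as r rises. For the six-visit analysis the larger loss is interpretive: a 5-df test yields no signed difference at a named visit. The dilution by 1/2 or 5/6 is plain arithmetic, but conditional on the main effect being read as the treatment effect, and the 5/6 also on a constant effect after T0. The uselessness of the baseline tests depends on no assumed figure.

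All of the T0 argument assumes that T0 enters as a level of time, a strong inference rather than a statement. The figures assume all 40 participants are analysed; the planned exclusion of incomplete cases would lower precision under either method.

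**What to change.** In Data Analysis, Statistical Power, and Sample Size:

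1. For each continuous secondary and tertiary outcome, report the T0-adjusted VSail minus WEB-Health difference at T1 with a 95% CI, from ANCOVA or from the T1 contrast of a mixed model with baseline as covariate.
2. Add the T2 to T5 contrasts from the same kind of model where those visits are measured. Sway area, gait and Timed-Up-and-Go stop at T1.
3. State that the group and time main effects are not evidence of benefit.
4. Replace the chi-square and 1-way ANOVA baseline tests with a descriptive table by arm.

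The cost is analysis wording and some reprogramming. The schedule already collects T0 for every secondary and tertiary outcome, so no new data are needed. The change does not concern satisfaction, dropout or the recruitment proportion, which have no baseline value to adjust for.

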## Methods

### Study Design

This study is designed as a feasibility RCT. Assessments will be conducted at the following time points: T0 (0 weeks - baseline), T1 (6 weeks), T2 (12 weeks from T1), T3 (24 weeks from T1), T4 (36 weeks from T1), T5 (48 weeks from T1). The study adopted a longitudinal, 2-arm design, with participants randomized to either an active interventional protocol based on the Virtual Sail 3D (VSail) experimental protocol or to a control setting, “WEB-Health” (education on healthy lifestyles to promote active aging). Participants will be independently randomized in a 1:1 ratio to one of the two parallel assignment groups: (1) VSail or (2) WEB-Health. The study protocol is written according to the CONSORT (Consolidated Standards of Reporting Trials) 2010 statement for randomized pilot and feasibility studies [28] (Figure 1).

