### Randomization and Allocation Concealment

Participants who meet the eligibility criteria will be randomly assigned to one of the two groups: an intervention group and a control group. Randomization will be conducted after baseline assessment. Randomization will be computer-based and concealed. The individuals conducting the randomization procedure will be blinded to participants’ identities and statuses and will not receive any information about them. Participants will be randomly assigned to experimental or control groups in a 1:1 ratio using block randomization. Allocation codes were concealed.

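### Excluding every case with missing data from the six-visit ANOVA limits the follow-up estimates of cognitive and questionnaire outcomes to completers

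*Protocol article*

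**What the plan says.** The rule is in the section on data analysis, statistical power and sample size: "Cases with missing data will be treated as incomplete and excluded from the analyses". The same paragraph sets out tests of group, time and their interaction, and says that "repeated-measures ANOVA and multivariate ANOVA will be applied to continuous variables".

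The Study Design section and Textbox 1 place all cognitive tests and all self-report questionnaires on psychosocial outcomes and physical activity at T0 to T5. T1 is at 6 weeks and T5 is 48 weeks after T1. Sway area, gait speed, Timed-Up-and-Go and the Simulator Sickness Questionnaire are taken at T0 and T1 only, and satisfaction at T1 only. The Results section schedules a pre-post analysis for January 2026 and completion of the follow-up analyses by January 2027.

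The article explains its many outcomes by the need to "obtain preliminary effect size estimates and variability parameters" for a later trial. On size it says that "a total sample of 40 participants (20 per arm) was considered appropriate to assess procedural feasibility, obtain reliable estimates of variability". It labels all secondary and tertiary analyses exploratory.

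**The concern.** Repeated-measures ANOVA and MANOVA need a full set of visits for each person. With six visits, a participant who misses one contributes nothing to that analysis, including the visits attended. The article fixes this rule itself, so it is not a detail left to a separate analysis plan.

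The article also gives reasons to expect missing visits. Dropout is a primary outcome. The Results section says that attendance and engagement were not always feasible at this age and with cognitive impairment. The arms differ in burden (12 headset sessions against 3 webinars), and the Risk and Benefits section lists dizziness, nausea and headache for the headset. Loss that differs by arm and is related to cognition is therefore plausible. At stake are the effect sizes and SDs that the next trial is to be planned on.

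**Working it through.** **Inputs from the article.** N = 40, 20 per arm. Six visits, of which five are post-baseline. Last visit at 6 + 48 = 54 weeks. No dropout rate, SD or target effect is stated, and the sample size rests on precedent, so there is no calculation to reproduce. All loss rates below are assumptions.

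**Step 1: who remains.** If a fraction *a* is missing at each post-baseline visit, independently across visits, the complete cases number 40(1 − a)^5. Those with a given visit, such as T1, number 40(1 − a). A model using every observed visit keeps 1 − 5a/6 of the planned measurements; the exclusion rule keeps (1 − a)^5.

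| a | Complete cases | With T1 data | Kept, all observed visits | Kept, exclusion rule |
|---|---|---|---|---|
| 3% | 34.3 | 38.8 | 97.5% | 85.9% |
| 5% | 31.0 | 38.0 | 95.8% | 77.4% |
| 10% | 23.6 | 36.0 | 91.7% | 59.0% |

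If a missed visit instead means permanent dropout, the complete cases are the same in number. The measurements observed are then [1 + (1 − a) + … + (1 − a)^5]/6 = 92.8%, 88.3% or 78.1%. In that case everyone seen at T5 is a completer, and what the rule discards is the earlier visits of those who left.

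**Step 2: precision.** The standard error of the group difference is 2/√n in SD units: 0.316 with 40 and 0.408 with 24. The 95% multiplier for a pooled SD widens from 0.82–1.29 (n = 40) to 0.77–1.42 (n = 24). A T1 contrast read from the six-visit model has its standard error raised by √[(1 − a)/(1 − a)^5] = (1 − a)^−2, that is by 6%, 11% or 23%.

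**Step 3: bias.** This was checked by simulation with 400,000 participants per arm, so the results show bias rather than chance. Assumptions: SD 1, correlation 0.5 or 0.7 between any two visits, true effect 0.30 SD at every post-baseline visit. The chance of leaving before each visit is logistic with intercept −3, and slope −1 on the last score where loss is score-related (0 otherwise). Total loss was 21% to 29% per arm.

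| Loss pattern | T5 difference | Difference in change, T0 to T5 | SD at T5 |
|---|---|---|---|
| Random in both arms | 0.30–0.31 | 0.30 | 1.00 |
| Low scorers leave both arms | 0.27–0.28 | 0.30 | 0.95–0.98 |
| Low scorers leave the VR arm, random in control | 0.42–0.46 | 0.27–0.28 | 0.96–0.98 in the VR arm |

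**Step 4: what this would do to the next trial.** Required n is proportional to (SD/difference)².

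- Low scorers leave both arms, using the T5 difference: (0.974 × 0.30/0.278)² = 1.10 at correlation 0.5 and (0.954 × 0.30/0.269)² = 1.13 at 0.7. The next trial would be 10% to 13% too large.
- Low scorers leave the VR arm only, using the pooled SD: (0.988 × 0.30/0.418)² = 0.50 and (0.979 × 0.30/0.459)² = 0.41. The next trial would have half the needed size or less.

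A group-by-time analysis is closer to the change column, where the bias is smaller: between none and about 10% (0.269 against 0.30).

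**The case against.** Much can be said for a milder view, and most of it stands.

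- **Scope.** A reader might infer that every estimate in the trial depends on completing six visits, and that T1 results lose their data too. The article does not support this. Recruitment runs to November 2025 and T5 falls 54 weeks after baseline, so an analysis in January 2026 cannot require T5 data from late entrants. The 6%, 11% and 23% figures apply only to a T1 contrast taken from the later six-visit model. Outcomes measured only at T0 and T1, and the counts of dropout and recruitment, are untouched by the six-visit loss. What remains is the follow-up analysis of the cognitive and questionnaire outcomes.
- **Direction.** A reader might infer that completers always look more stable and more alike, so the next trial must be too small. Step 4 shows the size error going either way. Larger distortions can be produced: one simulation with about 43% loss gave an SD 11% too small and control decline understated by 16%. But another with similar loss and different assumptions gave no understatement of decline and changed the implied size only between −3% and +5%. No dropout rate in the article lets one choose between them.
- **Purpose.** The analyses are exploratory, and no confirmatory conclusion depends on the rule. This lowers the severity. It does not excuse the rule, because effect sizes and variability are what these analyses are meant to deliver.
- **Remedy.** Dropout in the simulations depends on observed scores, which is the situation a mixed model handles best. No mixed model was fitted to the same simulated data, so its recovery of the true values rests on theory here.

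**Conclusion.** The point holds for the six-visit follow-up analyses of the cognitive and questionnaire outcomes. The stated rule, joined to repeated-measures or multivariate ANOVA, makes those estimates describe completers only. With 3%, 5% or 10% assumed missing per post-baseline visit, about 34, 31 or 24 of 40 remain. Under completely random loss the harm is lost precision and nothing more. If loss is related to outcome, effect and SD estimates can be biased upward or downward, depending on whether loss differs by arm and on whether the T5 difference or the change is read. The article does not say whether a case is incomplete per outcome or across the whole battery; the loss is larger in the second reading. This is a recommended improvement.

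**What to change.** For the outcomes measured at T0 to T5, replace the exclusion rule and repeated-measures ANOVA with a linear mixed model for repeated measures (SPSS MIXED). Include all observed visits of all randomised participants in the arm assigned, with visit as a factor, group-by-visit and adjustment for baseline. Start from an unstructured covariance and name in advance the simpler structure to be used if it does not converge. Non-convergence is a real possibility: six visits modelled jointly need 6 × 7/2 = 21 covariance parameters from about 40 people, or 5 × 6/2 = 15 if T0 enters as a covariate. Keep the complete-case results as a sensitivity analysis, and report missing data by arm and visit.

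The cost is changed wording and syntax in software already named, and a little more analysis work. No new data are needed, and the change can be made before the follow-up analyses are run. The price in assumptions is reliance on data being missing at random given the observed scores, which should be stated.
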